Evidence from two recent randomized controlled trials (RCTs) suggests that group PFMT is effective for treating stress and mixed UI in older women, resulting in high continence rates post-intervention compared to no treatment or bladder training [16, 17]. A group-delivery approach offers an effective way to overcome financial and human resource barriers; moreover, it has been shown to increase participant’s motivation, adherence, and UI self-management capabilities [18–22]. In recent years, the search for less costly forms of rehabilitative treatments has taken on a greater impetus and been subject to intense debate [8, 23, 24]. It is now recognized that for some pathological conditions, group rehabilitation approaches offer a viable solution, one that would permit better allocation of available economic resources—material and human [23]. Additionally, group intervention is already acknowledged, within the field of health promotion, as a powerful tool for promoting behavior modification: group sessions provide greater motivation (by reducing an individual’s sense of isolation) and a forum for providing information (particularly for those too timid to ask questions) and foster peer support and discussions: e.g. Weight Watchers [25]. Tackling UI through group sessions could also prove to be an effective means of educating and encouraging active self-management; therefore, it could have an impact in the longer term. [26, 27] To date, no studies have compared with adequate power the long-term effectiveness or cost-effectiveness of group PFMT to individualized PFMT for the treatment of UI in older women [18].

Given group PFMT’s promising results, there is a clear need to compare the short- and long-term effectiveness and cost-effectiveness of group vs individual PFMT, especially considering demographic projections, the high prevalence of UI in older women and the costly barriers to individualized PFMT. If we demonstrated that group-based treatment is not meaningfully less effective than individualized one-on-one treatment, and more cost-effective, group-based PFM training would be warranted as a first-line UI treatment.

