#### Group-based PFMT

The only specificity for this treatment group is that women participate in groups of eight in a weekly 1-h session, under the supervision of an experienced physiotherapist. They are also offered up to three optional private (20 min) sessions with the physiotherapist leading their group (either before or after a group session) to ensure understanding and correct performance of a PFM contraction – as confirmed by vaginal digital palpation [17]. This treatment approach is consistent with Bo’s PFM exercise class [54] and our more recent pilot cohort studies indicating it is both feasible and effective intervention for UI in aging women [18, 55]. In case of slow recruitment, we have established a minimum group size of six participants in order to avoid delays for those assigned to group physiotherapy.

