##### Sample size calculation

Sample size was calculated so as to ensure the adequate power and type I error rate for testing the primary hypothesis of non-inferiority of the group-based intervention relative to the individualized intervention, in achieving the relative reduction (in %) in the number of UI episodes at one year. Sample size calculations followed CONSORT Guidelines for non-Inferiority trials [68]. First, based on clinical relevance [69] (minimum clinically relevant difference = 10%) and our pilot data [18–22], we set the “margin of equivalence” (i.e. the upper limit of the non-inferiority interval) as corresponding to a 10% difference between mean % reduction in the number of UI episodes in the “standard treatment” of the individualized intervention minus the group-based intervention arm. This implies that we test the null hypothesis H0:d ≤ 10%, where d denotes the true difference between the mean relative reductions in the number of UI episode in the two arms (individualized minus group-based) against the alternative hypothesis H1:d > 10%. According to the CONSORT guidelines, this choice of the “margin of equivalence” implies that the non-inferiority hypothesis should be rejected whenever the upper bound of the two-tailed (1 – 2α)% confidence interval (CI) for the difference between the two mean % reductions exceeds 10%. In the specific context of a non-inferiority trial, α is the selected risk of a false acceptance of the non-inferiority hypothesis (based on a one-tailed CI-based test, equivalent to an independent-group t-test); i.e. of a false conclusion that a truly inferior intervention is equally efficacious as the “standard treatment” [68].

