To err on the conservative side, we relied on the “standard” 95% CI, which corresponds to a stringent one-tailed type I error rate of α = 0.025 (2α = 1–0.95 = 0.05). Similar to other recent non-Inferiority trials (e.g. [70, 71]) and CONSORT guidelines [68], for the purpose of sample size calculation, we assume that the true difference between the mean reductions (%) achieved by the two interventions will be zero (i.e. that they are equally effective). Note that this assumption of equivalence of the two interventions being compared in our trial is consistent with both (a) clinical expectations and (b) (limited) published evidence concerning young and middle-aged UI women [72–74]. Finally, both published trials, which evaluated similar interventions in older women, reported within-group standard deviations (SD) of the individual % reduction scores of about 27% [44, 75]. Accordingly, we assumed SD = 27% in our calculations.

Under the above assumptions, we estimated the sample size needed to ensure high (90%) power to demonstrate the non-inferiority of the group-based intervention (assuming, as mentioned above, that the true difference is 0%). Thus, we calculated N, for which the probability that the upper boundary of the two-tailed 95% CI for the difference in the mean relative reduction (Individual – Group) excludes the “upper threshold of non-inferiority” (10% difference), will reach at least 90%. The sample size calculations were performed using the program in the PASS software package, designed specifically for power/sample size estimation for non-inferiority trials [76]. Under the assumptions outlined above, we will need 155 participants per group, for a total of 310 individuals. We also need to account for possible losses to follow-up, as we expect a 15% attrition rate by the end of the one year, based on both our pilot data and similar published trials [16, 17, 22, 51]. Thus, we will recruit an additional 54 participants per group, increasing the total number of participants to 364 (364*(1–0.15) = 310).

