Analyses for the primary outcome at one year (and secondary outcomes): The primary analysis will test our main hypothesis that group-based classes are not inferior to individualized treatment with respect to the primary outcome of relative (%) reduction in the number of leakages at one year post randomization. (For all outcomes, the analyses outlined below will be repeated using data on post-intervention assessment.) As recommended for non-inferiority trials, the hypothesis of non-inferiority will be accepted if, and only if, the upper bound of the two-tailed (1-2α) 95% CI (corresponding to a conservative Type I error of 0.025 for the one-tailed independent-group t-test) for the mean difference (in % reduction) excludes the non-inferiority threshold [68], set at 10% difference. This basic analysis will be extended to multivariable analyses. Specifically, two multivariable linear models, of increasing complexity, will be used to adjust the estimated difference between the % reduction at one year in the two groups for, respectively, (1) only the two stratification variables (center and type of UI), as well as the baseline number of UI episodes (to account for regression to the mean phenomenon); and (2) (if necessary) in addition to variables in model (1): any variable, for which a clinically important imbalance between the two arms is revealed by descriptive analyses (see above). In both models, the two-way interactions between the trial arm and (a) center and (b) UI type, will be tested using 1-df model-based F-tests to verify if the difference between the effects of the two interventions depend on either of those stratification variables. In the case of a statistically significant interaction (*p* < 0.05 for the F-test), the intervention effects will be estimated and tested separately in the respective subgroups [79]. The results of multivariable linear regression analyses will be summarized in terms of adjusted mean difference between the outcomes in the two trial arms, together with the 95% model-based CIs. In sensitivity analyses for primary and secondary outcomes at one year, ITT analyses will be conducted, using the same statistical methods.

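### The group arm is treated in classes of six to eight, but the sample size and primary confidence interval assume independent women; if outcomes correlate within class, the one-sided error exceeds 0.025 and valid power falls below 90%

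*Protocol article*

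**What the plan says.** Delivery differs by arm. Under Group-based PFMT, "women participate in groups of eight in a weekly 1-h session, under the supervision of an experienced physiotherapist", with a minimum class size of six if recruitment is slow. Under Individualized PFMT, each woman is treated alone. Randomisation is by individual, stratified by centre and type of incontinence.

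The Sample size calculation describes the method as "based on a one-tailed CI-based test, equivalent to an independent-group t-test", uses a 95% interval that "corresponds to a stringent one-tailed type I error rate of α = 0.025", and aims for "high (90%) power to demonstrate the non-inferiority of the group-based intervention". With a margin of 10 points, a true difference of 0 and an SD of 27, it concludes that "we will need 155 participants per group, for a total of 310 individuals". The only inflation is for 15% attrition, to 364.

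The Data analysis section accepts non-inferiority if and only if the "upper bound of the two-tailed (1-2α) 95% CI" lies below 10 points, "corresponding to a conservative Type I error of 0.025 for the one-tailed independent-group t-test". The adjusted models add centre, type of incontinence, baseline episodes and any imbalanced covariate, with model-based intervals. The ITT analysis repeats the same methods. No class term, ICC or design effect appears anywhere.

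Two other places bear on this. The Background says that group sessions "foster peer support and discussions", and the rationale for the non-inferiority design expects peer support to raise compliance. Standardization of treatment has the same physiotherapist deliver both formats at a location.

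**The concern.** Women in one class share a timetable, a set of peers and a group dynamic for 12 weeks. If some classes do better than others for such reasons, the outcomes of classmates are correlated and the mean of the group arm is less precise than an independent-samples formula says. The individual arm has no counterpart, so the extra variance enters from one arm only.

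An interval that is too narrow brings the upper limit for individual minus group too low, which makes it easier to clear the 10-point margin. The error therefore favours the hypothesis that the trial was set up to support, and the protocol says that a positive result would warrant a change in clinical practice. The test and its accept/reject rule are stated outright, so this is a question about a stated choice and not about a detail left to an analysis plan.

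**Working it through.** **Inputs from the protocol.** One-sided alpha 0.025; margin 10; true difference 0; SD 27; 155 analysed per arm; attrition 15%; class size 8, minimum 6.

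**Assumed.** ICC of 0.02, 0.05 or 0.10 (none is given); the same total SD of 27 in both arms; 6 to 8 analysed women per class. A class of eight after 15% attrition leaves 8 × 0.85 = 6.8.

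**Step 1, the plan's own figure.** n per arm = 2 × [27 × (1.960 + 1.2816)/10]² = 153.2, so 154. The noncentral t version gives 155, with power 90.2%. The protocol's 155 is reproduced, but only under independence.

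**Step 2, standard error with classes in one arm.**
- Design effect in the group arm: DE = 1 + (m − 1) × ICC.
- Naive SE of the difference: 27 × √(2/155) = 3.067.
- True SE: 27 × √((1 + DE)/155).
- Ratio of true to naive SE: √((1 + DE)/2).

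**Step 3, error of the t-test as planned.** True one-sided error ≈ 1 − Φ(1.96/ratio). For m = 6.8 and ICC 0.05: DE = 1 + 5.8 × 0.05 = 1.29; ratio = √(2.29/2) = 1.070; 1.96/1.070 = 1.832; error = 0.0335.

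**Step 4, power of a valid analysis at 155 per arm.** With normal quantiles, power = Φ(10/true SE − 1.96). For m = 6.8 and ICC 0.05 the true SE is 3.282 and power is 86.2%. This is slightly optimistic, because the group-arm variance is estimated from few classes (155/8 = 19.4 to 155/6 = 25.8). Write V₁ = 27²/155 for the individual arm and V₂ = 27² × DE/155 for the group arm, with k classes. The Satterthwaite degrees of freedom are (V₁ + V₂)²/[V₁²/154 + V₂²/(k − 1)]. For m = 6.8 (k = 22.8) they run from about 76 at ICC 0 to 55 at ICC 0.10. Noncentral t power with these degrees of freedom is in the last column.

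| ICC | DE (m = 6 to 8) | SE ratio | One-sided error, planned test | Valid power, normal | Valid power, small-sample df |
|---|---|---|---|---|---|
| 0 | 1.00 | 1.00 | 2.5% | 90.3% | about 90% |
| 0.02 | 1.10-1.14 | 1.02-1.03 | 2.8-2.9% | 88.9-88.3% | 88-87% |
| 0.05 | 1.25-1.35 | 1.06-1.08 | 3.2-3.5% | 86.7-85.3% | 86-84% |
| 0.10 | 1.50-1.70 | 1.12-1.16 | 4.0-4.6% | 83.1-80.1% | 82-78% |

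**Step 5, simulation.** The planned t-test with 155 per arm and classes of 6 and 8 (20,000 runs per setting) gave errors of 2.6% and 2.6% at ICC 0, 2.9% and 3.0% at 0.02, 3.0% and 3.6% at 0.05, and 3.9% and 4.8% at 0.10. These agree with the formula within simulation error.

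**The case against.** The strongest reply is that no ICC is known and it may be small. Peer support as a general benefit of the format shifts the arm mean; only differences between classes create correlation. The programme is standardised with a checklist, training and supervised sessions, women also exercise at home five days a week, and the endpoint is an individual diary at one year, months after the classes end. All of this stands as a reason to expect a modest ICC. None of it makes the ICC zero, and the plan has no means of finding out.

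A reader might list the shared therapist as a source of correlation within the group arm. The protocol does not support that: the same physiotherapist treats both arms at a location, so therapist effects should largely cancel in the difference. Class-specific effects remain.

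A reader might also take the word conservative as a false claim of robustness. In context it describes the choice of a 95% interval, that is, a one-sided 0.025. The fair criticism is narrower: the stated 0.025 is exceeded if the ICC is positive. Within the assumed range it stays below 5%.

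Finally, an unadjusted t-test after stratified randomisation has too large a standard error if the strata predict outcome, which would offset part of the effect. That is true, but its size is equally unknown, and it does not replace modelling the classes.

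**Conclusion.** The point holds conditionally. The design is partially nested and the stated analysis ignores it. For any positive ICC the class effect makes the interval too narrow, and the one-sided error moves above 0.025 toward falsely declaring non-inferiority. The distortion is small at ICC 0.02 and material at 0.10, where the error is 1.6 to 1.8 times nominal and a valid analysis misses true non-inferiority about 18-22% of the time instead of 10%.

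It would go too far to say that the stated error and power are wrong outright: at ICC 0 they are right, and the documents give no ICC. The figures rest on the assumed ICC range, equal total SD in both arms and 6 to 8 analysed women per class. What is certain is the direction, and that the plan as written can neither detect nor correct the problem.

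**What to change.** - Record a coded class identifier for each woman in the group arm.
- Base the primary 95% interval on a class-adjusted method, chosen before analysis. One option is a linear mixed model with a random class intercept in the group arm only and Satterthwaite or Kenward-Roger degrees of freedom. The other is cluster-robust standard errors with a small-sample correction, each individually treated woman being her own cluster. Compare the upper limit with 10 points as now.
- Use the same structure in the adjusted models, the ITT analysis and the secondary outcomes.
- Restate power as conditional on the ICC: about 90% only if it is 0, about 87-88% at 0.02, 84-86% at 0.05 and 78-82% at 0.10. Report the estimated ICC with the results.

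No extra patients are needed, which matters with 353 of 364 already recruited. The cost is one data field, a change of wording, a slightly wider interval and a less favourable stated power. Because only one arm has classes, the identifier can reveal allocation to the blinded analysts, so it is best merged after the analysis code is fixed.

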##### Pre-treatment covariates

In order to be able to adjust for potential imbalances, across the two randomization groups, in the distributions of covariates, that may be potentially associated with the outcomes, baseline measurement of the following variables will be carried out: basic socio-demographic data including age, BMI, general health status, medical history and medications, parity and obstetrical history as well as type and duration of UI. In secondary analyses, we will then use multivariable regression models to adjust the between-groups differences in the outcomes for these covariates, in addition to the pre-treatment values of the respective outcome variable.

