#### Data analysis

General analytical strategy: as opposed to conventional superiority trials, in non-inferiority trials per-protocol analysis is generally preferable to intention-to-treat (ITT) analysis, because the postulated hypothesis being tested assumes no difference between the two interventions [68]. Indeed, in non-inferiority trials, a “conservative” approach relies on a per-protocol analysis, which maximizes the probability of finding a statistically significant difference between the two groups, i.e. of rejecting the hypothesis that has motivated the trial. Moreover, the ITT approach includes all individuals who were initially randomized, regardless of their adherence, and thus may dilute, or even mask, the true difference between the interventions in the case of non-adherence or losses to follow-up [59]. In the extreme, if most participants do not adhere to the assigned intervention or fail to complete the follow-up assessment, the ITT analysis will automatically show no difference. To prevent such paradoxes, our main analysis will rely on the per-protocol approach, i.e. include only participants who will have completed the one-year assessment. On the other hand, because of its popularity, we will use the ITT approach in “sensitivity analyses,” as recommended by the CONSORT guidelines for non-inferiority trials [68]. Furthermore, our analyses will focus on (primary or secondary) outcomes at one year. Because all primary and secondary outcomes are measured on continuous scales, the methods outlined below for the analyses of the primary outcome will also apply to all secondary outcomes. However, the analysis of secondary outcomes will be exploratory in nature and some (e.g. for PFM function) may have more limited statistical power.

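### The adjusted model for secondary outcomes is described in two ways: the Pre-treatment covariates section uses each outcome's own baseline, the Data analysis section names only the baseline leak count, and the covariate sets also differ

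*Protocol article*

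**What the plan says.** Two sections of the Protocol article describe the adjusted models.

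- **Pre-treatment covariates.** "In secondary analyses, we will then use multivariable regression models to adjust the between-groups differences in the outcomes for these covariates", and this is done "in addition to the pre-treatment values of the respective outcome variable". The covariates listed there include age, BMI, general health, medical and obstetrical history, and type and duration of UI. Centre is not named.
- **Data analysis.** Two linear models "will be used to adjust the estimated difference between the % reduction at one year in the two groups". Model (1) contains "1) only the two stratification variables (center and type of UI), as well as the baseline number of UI episodes", the last term being there "to account for regression to the mean phenomenon". Model (2), used if necessary, adds "any variable, for which a clinically important imbalance between the two arms is revealed by descriptive analyses".

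The Data analysis section also states that "the methods outlined below for the analyses of the primary outcome will also apply to all secondary outcomes". The lead-in to the paragraph holding the two models mentions secondary outcomes in parentheses. The same section notes that "the analysis of secondary outcomes will be exploratory in nature".

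**The concern.** For the primary outcome the two descriptions share the same baseline term, because the percent reduction is computed from the baseline leak count. For a secondary outcome they do not. If the Data analysis models are carried over as written, the pad test, the ICIQ scores, the self-efficacy scales, dynamometry and ultrasound are adjusted for baseline leaks and not for their own baseline. Nothing in the text says that the baseline term changes with the outcome. The stated reason for the term, regression to the mean, fits an outcome's own baseline. The leak count does not in general correct regression to the mean in pad weight or a quality-of-life score.

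The covariate sets differ as well: a stated list in one section, only variables found to be imbalanced in the other.

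At stake are the precision of the adjusted secondary estimates, their protection against modest chance imbalance, and the freedom to choose between two stated models after results are seen.

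**Working it through.** **The plan's own figure.** The article gives no SD, baseline-to-follow-up correlation or precision for any secondary outcome, so the only figure to reproduce is the number analysed. With margin 10, SD 27, true difference 0, one-sided alpha 0.025 and 90% power, the normal approximation gives 154 per arm. The noncentral t gives power of 89.97% at 154 and 90.15% at 155. The planned 155 per group is confirmed and is used below.

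**Assumed inputs (not in the article).**
- r: correlation of a secondary outcome at one year with its own baseline, taken as 0.3, 0.5 and 0.7.
- q: correlation of the same one-year value with the baseline leak count, taken as 0 to 0.4 and left free of r.

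**Formula.** With one baseline covariate, residual variance is proportional to 1 − r² (own baseline) or 1 − q² (leak count). Centre and UI type are common to the two fits compared and are left out. The ratio of interval widths, leak-count model over own-baseline model, is √[(1 − q²)/(1 − r²)].

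| r | q = 0 | q = 0.2 | q = 0.3 | q = 0.4 |
|---|---|---|---|---|
| 0.3 | 1.05 | 1.03 | 1.00 | 0.96 |
| 0.5 | 1.15 | 1.13 | 1.10 | 1.06 |
| 0.7 | 1.40 | 1.37 | 1.34 | 1.28 |

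Example: r = 0.5, q = 0.2 gives √(0.96/0.75) = 1.13. The ratio exceeds 1 only when r is larger than q, and it reverses at r = 0.3, q = 0.4.

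**Absolute size.** The 95% half-width with an uninformative covariate is 1.96 × √(2/155) = 0.223 SD. With the own baseline it is 0.223 × √(1 − r²) = 0.212, 0.193 and 0.159 SD at r = 0.3, 0.5 and 0.7.

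**Simulation check.** In 1,000 least-squares fits with 155 per arm, the mean standard error was 0.0985 SD (own baseline) against 0.1115 SD (leak count) at r = 0.5, q = 0.2, a ratio of 1.13. At r = 0.7, q = 0.3 it was 0.0810 against 0.1084, a ratio of 1.34. Both match the table.

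**Chance imbalance.** The standard error of the baseline difference between arms is √(2/155) = 0.114 SD. If an imbalance of that size is left unadjusted, and the leak count carries none of it, the estimate moves by r × 0.114, which is about 0.03, 0.06 and 0.08 SD at r = 0.3, 0.5 and 0.7.

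**The case against.** The strongest reply is that there is one rule, not two. The model sentence in Data analysis is written for the percent reduction, and for that outcome the leak count is the relevant pre-treatment value. The Pre-treatment covariates section then gives the general rule, and Data analysis shows its primary-outcome case. Carrying over methods need not mean carrying over every term specific to the primary outcome; otherwise the 10% margin would go with them. The regression-to-the-mean reason supports this reading. The covariate list can likewise be read as candidates, since its stated purpose is to allow adjustment for potential imbalances.

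This stands in part. A reader might infer a firm contradiction, but the documents do not support that, because a harmonious reading exists. It does not remove the point: the text never says that the baseline term changes with the outcome, and model (1) is limited by the word only.

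Two other stronger readings also fail.
- **Always wider intervals.** The direction depends on correlations that the article does not give. Tying the leak count's predictive value entirely to the own baseline would make it lose in every case, but that would be a further assumption. With q left free, the difference can vanish or reverse.
- **Biased or unprotected estimates.** Randomization leaves either model unbiased on average, and model (2) would admit an own baseline whose imbalance is judged clinically important. Only smaller imbalances stay unadjusted.

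It is also fair to say that the unadjusted comparison applies to secondary outcomes and is unaffected. The choice of baseline term might have been left to a statistical analysis plan, but here the article states it, in two ways.

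**Conclusion.** The point holds as a mismatch of wording with a modest statistical cost. Read literally, the two sections give different baseline terms for secondary outcomes that have a pre-treatment value, and different rules for further covariates.

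Using the leak count in place of the own baseline loses precision, and leaves smaller chance imbalances unadjusted, whenever the own baseline is the stronger predictor of the one-year value. I would expect that to be usual, but the article cannot confirm it. On the assumed correlations the excess width runs from nil or a few percent at r = 0.3 to more than a quarter at r = 0.7.

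The importance is minor. The secondary outcomes are exploratory, and the primary test, margin, sample size and unadjusted analyses do not change.

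**What to change.** In Data analysis, state that the baseline term in models (1) and (2) is the pre-treatment value of the outcome being analysed. For the primary outcome this remains the baseline number of UI episodes. For the PGI-I and satisfaction with treatment, which have no pre-treatment value, keep the baseline number of UI episodes. Centre and UI type stay in.

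In both Pre-treatment covariates and Data analysis, state one and the same rule for further covariates: either the listed set, or only those found imbalanced. Aligning the baseline term alone would leave that second difference open.

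The cost is a sentence or two in each section. The baselines are already part of the pre-intervention assessment, no new data are needed, and the primary analysis is unchanged. The wording should be settled before one-year results are examined by arm.
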